### 2.13. Participant Safety

All participants will be fully informed about the study protocol prior to participation. They will be asked to provide informed consent in writing. This process will be conducted at the very beginning of the trial process. Participants will be informed about and monitored for any potential adverse events of acupuncture treatment at each visit. Adverse events will be recorded on a worksheet and case report form. If a serious adverse event occurs, the case will be immediately reported to the clinical trial director and the IRB at Kyung Hee University Korean Medicine Hospital. If necessary, part of the trial will be halted until further instructions are available.

### 2.14. Confidentiality

All documents will be categorized by unique codes but not by participants' names to protect confidentiality. All participant identification information will be kept confidential and will only be viewable by researchers. All data and records will be securely locked under the administration's protection for three years after the publication of the trial results and then destroyed. The human-derived fecal and blood samples will be stored for as long as the participant agrees (Two years will be recommended).

### 2.15. Quality Control

All study researchers will receive centralized and unified training before the study and all the processes will be conducted under the SOP. This study will be performed under the monitoring of the Korean Medicine Clinical Trial Center at Kyung Hee University Korean Medicine Hospital and the AMSRC. If a protocol modification is required due to unanticipated problems, representatives of this study will discuss the matter fully for the appropriate steps.

## 3. Discussion

This will be a randomized clinical, practical, sham-controlled trial with participant and assessor blinding for AD patients. The RCT will include VA or SA sessions twice a week for 4 weeks. This treatment dose was determined based on our previous studies [7, 8].

AD patients participating in this RCT will be recruited if they have an objective SCORAD score of 10 to 40 points. The lower limit was set at 10 points because there must be enough skin symptoms to evaluate the effectiveness of acupuncture treatment. On the other hand, patients with severe AD will be excluded to allow them to continue or seek AD treatments other than acupuncture (which will be prohibited for study participants). These SCORAD score cutoffs are the same as the standards used in our previous studies [7, 8].

The acupoints will be PC6, LI11, and ST36, which are expected to improve skin symptoms, and ST43, GB41, and LI3, which are expected to act on GI symptoms [25–27]. The former three acupoints, PC6, LI11, and ST36, have been confirmed to improve skin symptoms in patients with AD in two previous studies [7, 28]. PC6 is not only an acupoint that can be used symptomatically for skin itching but is also known to have a positive effect on the stabilization of autonomic nerve function [29]. In addition, LI11 was found to improve itching and lichenification in patients with AD [30, 31]. ST36 is effective in regulating itching in various dermatitis diseases, including atopic dermatitis, and its representative mechanisms include negative feedback action on IL-33 and inhibition of mast cell degranulation [32–35]. In particular, the latter three acupoints (ST43, GB41, and LI3) were selected based on the Korean traditional acupuncture method, the Saam acupuncture [26]. The combination of ST43-GB41 is widely used in the clinical symptoms of the GI tract, especially in the upper GI tract. The combination of GB41-LI3 is used for lower GI symptoms [27]. In summary, the acupoints of our study are a treatment that can improve not only skin symptoms but also overall GI symptoms.

Therefore, in this study, we will confirm the activity of each region and the linkage through fMRI as the main indicator of the gut-brain axis. The difference in brain activity between patients with AD and healthy individuals is actively studied [28, 29], and our study will also investigate changes in activity before and after acupuncture. Additionally, the diversity of the gut microbiota and the dominant strain in AD patients have been discussed [39, 40]. In our study, the gut microbiota of the VA treatment group, the SA treatment group, and healthy controls will be compared. Moreover, as mediators connecting the brain and gut, hematologic indicators, TARC and ATX, will be measured together. Effector/memory CD4+ T cells play an important role in allergic diseases. TARC is produced in the intestinal endothelium and epithelial keratinocytes and is known to play a key role in the development and activation of Th2-type inflammatory mediators as well as inducing T-cell chemotaxis [41]. ATX is known to exhibit high mRNA activity in the brain, adipose tissue, ovaries, and small intestine [42], and it has been shown to cause pruritogenic-mediating activity through an ATX-lysophosphatidic acid signaling process in animal studies [43]. Based on these observations and facts, TARC and ATX will be evaluated as mediators that connect the brain, intestine, and skin. The collection and evaluation of these multifaceted data is an advantage of this study.

## Figures and Tables

**Figure 1 fig1:**
[figure not shown]
Study flowchart. The light-yellow area depicts the randomized controlled trial component, and the dark-yellow area depicts the cross-sectional component.

**Table 1 tab1:** Study schedule for the AD patient group.

Outcome values and intervention		Baseline assessment	Treatment period								Final assessment
			1-week		2-week		3-week		4-week		
AD symptoms	SCORAD assessment	●				●					●
	EASI assessment	●				●					●
	DLQI assessment	●				●					●

GI symptoms	Abdominal examination	●				●					●
	GSRS assessment	●				●					●
	TDS assessment	●				●					●
	Bristol stool scale	●				●					●
	AR assessment			●	●	●	●	●	●	●	●

Gut-brain axis	BDI STAI-X1, 2	●									
	fMRI image (tasks 1 and 3)	●									●
	Stool collection	●									●
	Blood collection	●									●

	Acupuncture treatment		●	●	●	●	●	●	●	●	

	Investigate for adverse events		●	●	●	●	●	●	●	●	●

BDI, Beck Depression Inventory; STAI, State-Trait Anxiety Inventory; SCORAD, Scoring Atopic Dermatitis; VAS, Visual Analog Scale; EASI, Eczema Area and Severity Index; DLQI, Dermatology Life Quality Index; GSRS, Gastrointestinal Symptom Rating Scale; TDS, Total Dyspepsia Symptom Scale; AR, adequate relief of functional dyspepsia pain and discomfort; AD, atopic dermatitis. Except for the fMRI session, the baseline assessment will take between 30 minutes and 1 hour. An fMRI session, performed at the first and last evaluations, will take about an hour and a half to two hours. Each acupuncture session will take about 15 to 20 minutes. And a total of 30 to 45 minutes will be required for the questionnaires administered in the intermediate and final evaluations. Visit window is ±5 days. Baseline assessment—first acupuncture treatment and eighth acupuncture treatment—Endpoint assessment will be performed within 7 days. The visit window period is ±5 days.

**Table 2 tab2:** Study schedule for the healthy controls.

	Measurements	Assessment	Optional assessment (*n* = 25)
Gut-brain axis	BDI STAI-X1,2	●	
	fMRI image (tasks 1 and 3)	●	
	fMRI image (task 2, *n* = 25)		●
	Stool collection	●	
	Blood collection	●	

BDI, Beck Depression Inventory; STAI, State-Trait Anxiety Inventory. Except for the fMRI session, the baseline assessment will take between 30 minutes and 1 hour. An fMRI session will take about an hour and a half to two hours.

**Table 3 tab3:** Revised STRICTA checklist.

Item	Detail
(1) Acupuncture rationale	(1a) Style of acupuncture (i) Manual acupuncture (1b) Reasoning for treatment provided, based on historical context, literature sources, and/or consensus methods, with references where appropriate (i) Through a previous study conducted by this research team, it was confirmed that AD patients could be treated with acupuncture twice a week for 4 weeks to improve symptoms. In addition, the Acupuncture and Meridian Science Research Center textbook was referenced. Optimal acupoints were selected through clinical experience and consensus by the experts in acupuncture and AD optimal acupoints. (1c) Extent to which treatment was varied (i) No other interventions other than acupuncture.

(2) Details of needling	(2a) Number of needle insertions per subject per session (mean and range where relevant) (2b) Names (or location if no standard name) of points used (uni/bilateral) (i) Fixed points: 6 acupoints with 9 needles per participant per session: (ii) PC6, LI11, ST36 bilaterally, ST43, GB41, LI3 contralaterally (2c) Depth of insertion, based on a specified unit of measurement or on a particular tissue level from 5 to 30 mm, perpendicular to skin surface (2d) response sought (e.g., de qi or muscle twitch response) “De qi” sensation (2e) Needle stimulation (e.g., manual, electrical), manual stimulation, needle rotation with thumb and index fingers for the first 10–15 seconds No other stimulation sensations. (2f) Needle retention time 15 minutes (2g) Needle type (diameter, length, and manufacturer or material) A sterilized stainless steel needle (0.25 × 40 mm, Dong Bang Acupuncture Inc., Bundang, Seongnam, Korea)

(3) Treatment regimen	(3a) Number of treatment sessions (i) 8 sessions (3b) Frequency and duration of treatment sessions (i) Twice a week for 4 weeks, 15 minutes for each session (ii) Visit window: ± 5 days

(4) Other components of treatment	(4a) Details of other interventions administered to the acupuncture group (e.g., moxibustion, cupping, herbs, exercises, lifestyle advice) (i) Lifestyle advice will be given to all participants (ii) Any other interventions will be prohibited during the study period (4b) Settings and context of treatment, including instructions to practitioner and information and explanations to patients (i) Participants will be informed about acupuncture treatment in the study as follows: “In this study, you will be randomly allocated to the VA group or SA group. Acupoints will be selected as guided by traditional Korean medicine textbooks and AD-related reports.”

(5) Practitioner background	(5) Description of participating acupuncturists (qualification or professional affiliation, years in acupuncture practice, other relevant experience) (i) Acupuncture treatment in this study will be performed by a KMD who is majoring under the guidance of a Korean medical dermatologist. The clinical experience of this KMD is more than 2 years. The practitioner KMD will have to undergone more than 10 hours of training and simulation workshopping to ensure that he is able to provide consistent acupuncture treatment in accordance with a predefined protocol.

(6) Control and comparator interventions	(6a) Rationale for the control or comparator in the context of the research question, with sources that justify this choice (i) A control group (SA group) will be treated with sham acupuncture (SA) using park sham acupuncture Needles. (6b) Precise description of the control or comparator. If sham acupuncture or any other type of acupuncture-like control is used, provide details as for items (1) to (3) above (ii) Park sham acupuncture needles and devices will be used in the same environment as in the VA group. However, acupoints will be different: a Point 1 to 2 cm proximal and 1 cm medial to PC6, a point 1 cm proximal and 1 cm medial to LI11, and a point 1 cm proximal and 1 cm lateral to ST36, each bilaterally.

STRICTA: Standards for Reporting Interventions in Clinical Trials of Acupuncture; AD: atopic dermatitis; VA: verum acupuncture; SA: sham acupuncture; KMD: Korean medicine doctor.

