## Abstract

Atopic dermatitis (AD) is a relapsing and remitting chronic inflammatory skin disease for which a variety of etiological factors are involved. Treatment strategies should be multifaceted and have few side effects. In this respect, acupuncture has become increasingly popular as a safe, consistently effective, and drug-free therapy that treats multiple AD symptoms. We aim to not only verify the effectiveness of acupuncture but also suggest patient-specific response determinants and a new underlying mechanism implicating the gut-brain axis. We have designed a randomized, participant-blinded, sham-controlled clinical trial for 60 mild to moderate AD patients. In a previous study, we observed that the clinical skin symptoms of AD were closely associated with gastrointestinal (GI) symptoms. From these findings, we developed an intervention with six acupuncture points: three for AD symptoms and three for GI symptoms. Also, since high responders and low responders to the acupuncture treatment could be identified in the previous study, we now aim to explore response-determining factors, with a particular focus on GI symptoms. Therefore, we will precisely evaluate not only AD symptoms using the SCORAD, EASI, and DLQI tools, but also GI symptoms using the GSRS, TDS, BSFS, and AR tools and abdominal examination. AD develops in association with complicated pathophysiological factors, such as skin barrier function, genetic susceptibility, and immunological factors. Moreover, the underlying mechanism by which acupuncture treatment works has not been clearly elucidated. We, therefore, will conduct a simultaneous cross-sectional study with a sample of 40 healthy individuals, wherein potential indicators, such as fMRI, gut microbiota, and serum TARC and ATX, will be investigated to determine the gut-brain axis-associated mechanism of acupuncture. We expect that the results of this study could provide important clinical evidence for the effects of acupuncture and help elucidate the therapeutic mechanisms that underlie acupuncture's efficacy in AD treatment. This trial is registered with https://clinicaltrials.gov/ct2/show/KCT0005422 (Trial registration: Korean Clinical Trial Registry (http://cris.nih.go.kr; registration number: KCT0005422); date of registration: September 23, 2020).

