## 1. Introduction

Atopic dermatitis (AD) is a relapsing and remitting, inflammatory, chronic skin disease that is characterized by severe itching and eczema [1]. Its prevalence varies widely according to geographic location, but according to an International Study of Asthma and Allergies in Childhood (ISAAC)-based report, it is on the rise worldwide, with a global prevalence of approximately 230 million [1, 2]. Additionally, the factors involved in AD pathophysiology are complex and diverse, and recent focus has mainly been on the hygiene hypothesis, loss-of-function mutations of the FLG-encoding gene, environmental factors, and the gut microbiota-skin axis [3].

However, AD cannot be cured [3]. Therefore, multistep guidelines have been outlined to control symptoms and maintain remission for as long as possible. However, in clinical practice, many patients do not respond properly to existing treatments. Persistent, recurring skin symptoms also exist because of treatment discontinuity. On the other hand, if continuous systemic treatment is administered, concerns about side effects and complications come to the forefront [4]. Therefore, to cope with the limitations of these existing treatments, the potential role of East Asian medicine, including Korean medicine, is being actively studied [5, 6]. A recent paper reported that acupuncture is a safe AD treatment that can be effective at improving itchiness, Eczema Area and Severity Index (EASI) scores, and other global symptoms [6].

Our research team has conducted previous randomized controlled trials (RCTs) addressing AD-related topics [7, 8]. Thirty-eight patients with AD were recruited, divided into two groups, and treated with verum or sham acupuncture twice a week for 4 weeks. In that study, acupuncture was performed on three fixed acupoints (ST36, LI11, and PC6 bilaterally) and two additional points. Additional points were selected on an individualized basis according to the accompanying symptoms, such as ST43 and GB41 for gastric stiffness and tenderness or LI2 and GB31 for diarrhea and constipation. Through this study, we not only confirmed the effectiveness of acupuncture treatment but also highlighted two notable implications. The first was that AD severity and the presence of gastrointestinal (GI) symptoms were positively correlated, and the second was that some patients exhibited clear improvements, but some patients did not.

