#### 2.2.2. Cross-Sectional Component

The cross-sectional component will include 40 healthy controls and 60 patients with AD. The study will be conducted at the Kyung Hee University Korean Medicine Hospital and KUBIC.

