#### 2.11.2. GI Symptom Assessments

*(1) Abdominal Examination*. Abdominal examination is a commonly used diagnostic method in Korean medicine. Abdominal examination in Korean medicine differs from the physical abdominal examination of Western medicine because the Korean variation follows the Korean medical theory that specific responses appear at the body surface (abdomen) when the disease exists inside the human body. Therefore, in this study, we will use abdominal examination to detect GI symptoms [16]. Specific details include evaluation of tenderness in CV12 and ST25 on both sides and confirmation of the presence of stuffiness below the heart (*Simhabi, 心下痞*) and stuffiness and rigidity below the heart (*Simhabikyung,* 心下痞硬). Both *Simhabi* and *Simhabikyung* are symptoms that occur in the anticardium (the area encompassing CV13 and CV14). The former, *Simhabi*, includes the patient's feeling of fullness, bloating, stuffiness, and blockage in the epigastric region, which is felt only subjectively, but there is no objective resistance or tenderness. It includes all kinds of stomach upset, epigastric fullness after meals or as usual. *Simhabikyung* refers to a case in which a doctor can sense resistance in the epigastric region objectively by hand [17, 18].

*(2) Gastrointestinal Symptom Rating Scale (GSRS)*. The GSRS can be used to evaluate both upper and lower GI symptoms. In addition to pain, soreness, and indigestion affecting the upper GI tract, the characteristics of the stool and discomfort can also be evaluated together [19].

*(3) Total Dyspepsia Symptom Scale (TDS)*. The TDS is a tool used primarily for evaluating symptoms in patients with functional dyspepsia, particularly postprandial bloating, premature satiety, nausea, vomiting, and belching [20].

*(4) Bristol Stool Form Scale (BSFS)*. The BSFS is a proper tool in daily clinical practice. It is a quick, easy, and intuitive patient-reported measure of whole-gut transit time, and it can be used as a substitute for stool consistency [21].

*(5) Adequate Relief of Functional Dyspepsia Pain and Discomfort (AR)*. The content is as follows: “Have you experienced appropriate relief (more than 50% reduction) of the pain or discomfort associated with your dyspepsia after the last acupuncture treatment?” AR asks about the degree of improvement in general and nonspecific digestive discomfort [7].

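### Healthy controls have no GI-symptom or stool-form measure, so the part of the AD-healthy difference that is independent of GI symptoms cannot be estimated directly

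*Protocol article*

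**What the plan says.** Two schedules stand next to each other under Figures and Tables.

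- Table 1, "Study schedule for the AD patient group", has a separate GI block. Abdominal examination, GSRS, TDS and the Bristol stool scale are done at baseline, in week 2 and at the final assessment.
- Table 2, "Study schedule for the healthy controls", has only the gut-brain block: BDI/STAI, fMRI (with an optional extra task for 25 controls), one stool sample and one blood sample.

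The disease-specific entry criterion for controls in Section 2.4.1 is absence of AD. The diseases named as examples in Section 2.4.2 are mainly neurological or psychiatric, and no GI condition or symptom is named.

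The controls serve the mechanistic objective. Section 2.2.2 states: "The cross-sectional component will include 40 healthy controls and 60 patients with AD". The Abstract says of this component that "potential indicators, such as fMRI, gut microbiota, and serum TARC and ATX, will be investigated to determine the gut-brain axis-associated mechanism of acupuncture". The Discussion says that "the gut microbiota of the VA treatment group, the SA treatment group, and healthy controls will be compared", and Section 2.12.2 plans random forest and support vector machine models that identify the AD group.

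On GI symptoms, the Introduction reports from the group's earlier trial that "AD severity and the presence of gastrointestinal (GI) symptoms were positively correlated". Section 2.11.2 calls the BSFS a "quick, easy, and intuitive patient-reported measure of whole-gut transit time".

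**The concern.** The protocol expects GI symptoms to go with AD and treats stool form as a marker of transit. It then compares stool microbiota, serum markers and brain activity between a group in which these are measured and a group in which they are not. A feature that separates patients from controls could reflect AD, GI symptoms that accompany AD, or both. With no GI data on controls, the planned contrast cannot be adjusted, matched or stratified for them.

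At stake is the interpretation of the cross-sectional component and of the AD-discrimination models, which serve the second objective. A feature might be reported as belonging to AD when it would be found in anyone with dyspepsia or altered stool form.

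**Working it through.** **What is measured where**

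| Item | AD patients (Table 1) | Healthy controls (Table 2) |
|---|---|---|
| Stool, blood, fMRI, BDI/STAI | yes | yes |
| GSRS, TDS, BSFS | yes | no |
| Abdominal examination | yes | no |
| GI symptoms named in eligibility criteria | no | no |

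The Discussion's subgroups by presence or absence of GI symptoms cover only the 60 AD patients. The covariates named for the fMRI correlations in Section 2.12.2 are AD severity and group.

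**How large the effect could be**

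The protocol states no figure to reproduce. The group sizes of 40, 20 and 40 rest on expert agreement (Section 2.2.3), with no alpha, power, effect size or SD. What follows is an illustration.

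Inputs:
- From the protocol: 60 AD patients and 40 controls.
- Assumed: GI-symptom prevalence 0 to 40 percentage points higher in AD than in controls; a marker that differs by 0.5 to 0.8 SD between people with and without GI symptoms; no AD effect other than through GI symptoms; a two-sided 5% test of two means.

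Steps:
1. SE of the contrast = sqrt(1/60 + 1/40) = 0.204 SD.
2. Difference due to GI symptoms = prevalence gap × marker effect. No gap: 0. Gap 20 points, effect 0.5: 0.20 × 0.5 = 0.10 SD. Gap 40 points, effect 0.8: 0.40 × 0.8 = 0.32 SD.
3. Standardised: 0.10/0.204 = 0.49 and 0.32/0.204 = 1.57.
4. Two-sided rejection: 5% with no gap, 7.8% at 0.10 SD, 34.8% at 0.32 SD.

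For scale, 60 versus 40 has 80% power for (1.960 + 0.842) × 0.204 = 0.57 SD.

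**Simulation check**

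The unadjusted column uses 20,000 simulated studies per row and the other rejection columns 3,000. The outcome SD is 1 within GI strata, so the overall SD is slightly above 1 and the top rejection rate is 30.5% instead of 34.8%.

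| GI prevalence, AD / control | Marker effect (SD) | Difference due to GI (SD) | Rejection, unadjusted | Rejection, GI measured in both and adjusted | GI-negative AD vs all controls: bias (SD), rejection |
|---|---|---|---|---|---|
| 30% / 30% | 0.5 | 0 | 4.8% | 4.6% | -0.15, 9.9% |
| 30% / 30% | 0.8 | 0 | 4.9% | 5.0% | -0.24, 17.8% |
| 30% / 10% | 0.5 | 0.10 | 7.9% | 5.1% | -0.05, 5.8% |
| 30% / 10% | 0.8 | 0.16 | 11.1% | 5.4% | -0.08, 6.3% |
| 50% / 30% | 0.5 | 0.10 | 7.5% | 5.3% | -0.15, 8.4% |
| 50% / 30% | 0.8 | 0.16 | 11.3% | 4.9% | -0.24, 14.7% |
| 50% / 10% | 0.5 | 0.20 | 15.9% | 4.4% | -0.05, 5.2% |
| 50% / 10% | 0.8 | 0.32 | 30.5% | 4.8% | -0.08, 5.5% |

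Adjustment needs GI status in both groups, which Table 2 does not provide. The last column is the best contrast available under the current schedule. Its bias is minus the marker effect times the control prevalence. It is small if 10% of controls have symptoms and not small if 30% do, and the data will not show which case applies.

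**The case against.** The strongest objection is that GI symptoms may belong to AD. The Discussion describes a Th2 reaction in the duodenal mucosa of people susceptible to AD that leads to GI pain and delayed gastric emptying. On that account GI symptoms lie on the pathway, the unadjusted contrast is a valid total difference, and a difference that runs through them is not an error. Adjustment then answers a different question and brings its own assumptions. This stands. The protocol also states no aim of separating AD from GI symptoms in this contrast. But anyone who wants to know whether a marker goes with AD apart from GI symptoms needs the control data.

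Other objections:

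- The correlation in the Introduction is between severity and GI symptoms among enrolled AD patients. It gives no AD-versus-healthy prevalence gap. This stands, and is why the range starts at zero.
- A two-sample test of one marker does not represent PERMANOVA or the machine-learning models. This stands; the figures show direction and scale only.
- Table 2 may not list everything collected: the pre-scan sensory measures in Section 2.11.3 are in neither schedule. This is a fair caution. But Table 1 has a whole GI block that Table 2 lacks, and the GI instruments are described only as clinical outcomes of the AD patients.

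A reader might infer that GI symptoms are the only link between gut and skin and that it is missing in controls. The documents do not support this: the Introduction and Discussion name TARC and ATX as links, and blood is drawn in both groups. A reader might also infer that no later analysis can help. That goes too far: GI-marker associations can be estimated within the AD patients, and GI-negative AD patients can be compared with all controls. Both are partial remedies.

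**Conclusion.** The point holds as a limit on interpretation that is cheap to remove. Under the published schedule, the AD-healthy contrast in microbiota, serum and fMRI markers is interpretable as a total difference. How much of it is independent of GI symptoms or stool form cannot be estimated directly, because control GI status is unknown.

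The size is unknown. Under the assumed ranges above, 0 to 0.32 SD would be due to GI symptoms, with rejection about 5% to 35% of the time. It would be wrong to read the upper figure as the false-positive rate of the study: the inputs are assumed, equal prevalence gives no distortion, and a rejection is a false AD finding only if GI symptoms are not part of the AD pathway.

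The comparison of verum with sham acupuncture and the response-determinant analysis within the verum group do not use the controls and are unaffected.

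**What to change.** Add GSRS, TDS and BSFS, collected prospectively, to the single healthy-control visit in Table 2. Then report:

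1. the AD-control difference unadjusted, labelled as the total difference;
2. the same difference adjusted for GSRS and BSFS, labelled as the GI-independent difference;
3. a sensitivity analysis of GI-negative AD patients against GI-negative controls, with one definition of GI-negative, based on the questionnaires, applied to both groups.

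Do not ask controls already seen to fill in the forms from memory. Recalled values in controls set against current values in patients would put differential measurement error into the adjustment variable. Treat their GI status as missing and limit the interpretation accordingly. If the instruments cannot be added at all, say in the report that AD-control differences are total differences and may include GI symptoms.

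Cost: a few minutes for each of up to 40 controls at a visit they already attend, and a minor protocol amendment with ethics approval. No extra staff or procedure is needed. Both tables allot 30 minutes to 1 hour to the non-fMRI baseline assessment, although AD patients complete seven more assessments in it, so the control visit appears to have room.
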